## **Secondary outcomes**

Secondary outcome measures are:

- the headache index (Intensity x Frequency) after 6 and 12 months, where intensity is the sum of intensity of the daily pain in a month divided by number of days with headache and frequency is number of days with headache in a month.

Further secondary outcome measures are:

- the frequency of analgesic drug consumption after 6 and 12 months
- the frequency of headache (neck and shoulder pain) after 12 months

## **Inclusion and Exclusion criteria**

All the subjects employed at the Municipality of Turin at September, 2007 will be recruited.

Before starting the study, subjects will have to give via web informed consent to participate in the study according to the protocol for data collection (web-based).

Because of the pragmatic design, no exclusion criteria are required for this study.

## **Study duration**

Data from workers will be collected for 13 months (from October 1st, 2007 to October 31st, 2008)

## **Ethical aspects**

This study is oriented to a working community of healthy subjects who individually accept to participate and is totally non invasive (participants will only be instructed with explanations, video projections and printed material how to perform some simple neck and shoulder exercises and how to keep their cranio-cervical muscles reasonably relaxed during the day).

Given the very extensive size of the eligible population acceptance after informed consent and data will be collected via web. To this purpose all participants will receive a personal password and the data will be protected taking account of the suggestions of the legal section of the San Giovanni Hospital. In particular the informatic tools are as follows:

### **WINDOWS SERVER 2003**

This operating system specific for servers improves security for Web transactions

- isolating individual Web application,
- preventing applications from disrupting the Web services or other Web applications on the server
- preventing application failures,
- providing health-monitoring capabilities
- including internal firewall

This is also possible through services included as

- IIS 6.0 (**Internet Information Services**), well known group of services now improved.
- CLR (**Common language runtime**): a software engine that verifies that applications can run without errors and checks security permissions to ensure that code only perform appropriate operations.

### **SQL Server**

Database is based on **SQL Server security model** passing through two stages of authentication: one at the SQL Server level and the other at the database level.

Login names are maintained within the master database in order to make possible the backup after adding new logins to SQL Server. SQL Server logins are associated with user accounts and SQL server provides Authentication through both **Windows authentication mode** and a **Mixed mode**.

### **ASP.NET**

It's an application based on security operations that involves 3 fundamental steps:

- **Authentication:** the process of validating the identity to accepting credentials (e.g. username and password). Requests from the same user ideally are not subject to the authentication process until the user logs out of the web application.
- **Authorization:** users authenticated are allowed to access specific resources.
- **Impersonation:** this process enables an application to ensure the identity of the user and enables a server process to run using the security credentials of the client so that the ASP.NET applications are capable to execute the identity of client on whose behalf they are operating.

## Schedule

After informed consent, all participants will be asked to submit data relative to the presence and characteristics of headache and neck and shoulder pain (September 2007), and to keep a diary (web-based) for one month (October 2007, baseline period).

The participants will be randomized (cluster-randomization) in two groups (study and control group) according to departments distribution (September-October 2007).

At month 2 (November 2007) an instruction program will be administered to the study group only. The intervention consists of brief shoulder and neck exercises to be performed several times a day, a relaxation exercise and instructions of how to reduce hyperfunction of the craniofacial and cervical muscles during the day (see: Intervention).

The control group, instead, will not receive any cognitive program.

Both groups will again fill in the diary during month 7 (April 2008).

At beginning of month 8 (May 2008, beginning of the second phase of the study), the same instruction program (Intervention) will be administered to the control group.

Both groups will again fill in the diaries during month 13 (October 2008, end of the study).

The study design according to time flow is reported in Fig.1

[figure not shown]

Fig.1 . Study design

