### **Study design**

This is a controlled, cluster randomised, interventional trial conducted on the local government employees of the Municipality of Turin. The participants will be distributed in two groups according to local departments distribution. The eligible source population consists of 11780 workers in 444 departments. A cluster-randomised design will be employed to assign the eligible population in two groups (study and control group) stratified for professional groups and number of participants.

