### **Statistical analysis**

Subjects who will not give informed consent or will not complete the baseline diary (month 1) will be excluded from the analysis. The data will be analysed according to group distribution.

The **principal analysis** will be conducted between intervention and control group for the first phase of the study (months 1-7; Figure 1, line 1).

Analyses will be performed on subjects for which diaries will be completed for months 1 and 7.

The proportion of subjects with more than 50% reduction in headache days (and in neck and shoulder pain days) at the end of the study period will be assessed and compared between the two groups accounting for the cluster-randomized design of the study.

For each subject, the difference (Delta) in the frequency of symptoms between months 7 and the baseline (month 1) will be calculated; the Deltas between the two groups will be compared with parametric and non-parametric tests, where appropriate, taking into account the cluster-randomized design of the study.

Possible baseline differences between the study group and the controls will be evaluated with parametric and non-parametric tests where appropriate; unbalanced factors will be taken into account in the analysis, if necessary.

Explorative subgroup analyses will be performed by age, gender, severity, compliance, diagnosis, and type of job activity.

A **secondary analysis** (Figure 1, line 2) will be conducted within the intervention group, in order to evaluate the persistence of the efficacy of the intervention; the frequency of pain at months 13 will be compared with that observed at months 7.

A further secondary analysis will be conducted in order to compare the efficacy of the program in the intervention group (end of phase 1) and in control group (end of phase 2).

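### Randomisation is dated to overlap the October baseline diary, with no rule that allocation waits for the diary to close or is withheld until then

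*Protocol*

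**What the plan says.** The Schedule section of the Protocol places consent and a symptom questionnaire in September 2007. Participants are then asked "to keep a diary (web-based) for one month (October 2007, baseline period". On allocation it says: "The participants will be randomized (cluster-randomization) in two groups (study and control group) according to departments distribution (September-October 2007". Exposure to the programme begins afterwards: "At month 2 (November 2007) an instruction program will be administered to the study group only". The control group receives the same programme in May 2008.

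The Study design section describes the allocated population differently. It will "assign the eligible population in two groups", stratified by professional group and by how many people take part.

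The Statistical analysis section makes the October diary a condition of being analysed: "Subjects who will not give informed consent or will not complete the baseline diary (month 1) will be excluded from the analysis". It also defines Delta as the change in symptom frequency from month 1 to month 7. The Primary outcome section limits the responder measure to people with more than 4 pain days in the baseline period and requires a reduction of more than 50%. Data collection is by a daily diary that participants complete themselves.

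**The concern.** In a cluster trial with an open intervention, everyone in a department shares one allocation. If it is announced early, it reaches all of them. People who know they will be taught the exercises in November, and people who know they will wait until May, may differ in how diligently they keep the October diary and in how many pain days they record.

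The October diary does three jobs here:

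- It decides who enters the analysis.
- It decides who belongs to the responder denominator.
- It is the starting value for both the percentage reduction and Delta.

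A baseline influenced by allocation would therefore reach both primary measures. The Statistical analysis section allows adjustment for baseline factors found to be unbalanced. That does not repair selection on unmeasured factors or a distorted starting value. The order of consent, baseline and allocation is a design step, and an analysis plan cannot restore it once departments know their arm.

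**Working it through.** **Timeline from the Schedule section**

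| Step | Date |
|---|---|
| Consent and symptom questionnaire | September 2007 |
| Baseline diary | October 2007 |
| Randomisation of departments | September-October 2007 |
| Instruction, study group only | from November 2007 |

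The randomisation window contains the whole diary month. Instruction starts after it, so any influence on the baseline must come through knowledge of allocation, not through exposure to the programme.

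**The plan's own power figure.** The inputs are from the Sample size and Study design sections: 11780 workers, 20% participation, 444 departments, 50% symptomatic, 20% versus 10% responders, intracluster correlation 0.15, two-sided alpha 0.05.

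- Participants: 11780 × 0.20 = 2356, or 1178 per arm.
- Symptomatic per arm: 1178 × 0.5 = 589.
- Participants per department: 2356 / 444 = 5.31.
- Design effect: 1 + (5.31 − 1) × 0.15 = 1.646.
- Effective number per arm: 589 / 1.646 = 357.8.
- Power for two proportions: 0.964, or 0.955 with continuity correction, against the stated 0.95.

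The stated power reproduces. Equal loss of 10%, 20% or 30% in both arms would leave it at about 0.955, 0.943 or 0.926. The issue is bias, not power.

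**Unequal diary completion (assumed rates, not in the Protocol).** With 80% completion in one arm and 70% in the other:

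- Lost: 1178 × 0.20 = 236 and 1178 × 0.30 = 353.
- Excess lost in one arm: 1178 × 0.10 = about 118.

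A count of people lost is not itself a bias. It becomes one only if completion is related to outcome.

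**From selection to bias (assumed rates).** Suppose there is no true effect and 10% respond in both arms. In one arm completion is unrelated to response. In the other, a fraction a of would-be responders and b of non-responders complete the diary. The observed responder rate there is 0.10a / (0.10a + 0.90b).

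| a | b | Observed rate | Bias |
|---|---|---|---|
| 0.90 | 0.80 | 11.1% | +1.1 points |
| 0.90 | 0.70 | 12.5% | +2.5 points |
| 0.80 | 0.60 | 12.9% | +2.9 points |

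The planned difference is 10 points.

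**Misreported baseline days.**

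- A true 6-to-3 change is (6 − 3) / 6 = 50%, which is not a response under the primary definition of more than 50%. Reported as 7-to-3 it is (7 − 3) / 7 = 57%, a response. Delta moves from −3 to −4.
- A true 4 days reported as 5 moves a person into the symptomatic denominator.

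**The case against.** The strongest reply is that harm requires disclosure, and nothing in the Protocol says departments or participants learn their arm before November. In month 1 both groups have the same task, the web diary. A list drawn in October but not announced would cause none of this bias, and randomisation could fall in the last days of the month. All of that stands, so the risk is conditional. Fig. 1, the time-flow figure, is not shown in the text at hand, so it could not be checked for a stricter order.

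A reader might also infer that departments are allocated before anyone consents, so that joining itself could differ by arm. The Study design wording, "A cluster-randomised design will be employed to assign the eligible population in two groups (study and control group", invites that reading. The rest of the document leans the other way. The same sentence stratifies by how many take part, which is most naturally known only after people have joined. The Schedule starts from informed consent and then randomises participants. The Inclusion and Exclusion criteria require consent before the study starts. If consent does come first, leaving out those who refuse is not an exclusion after allocation. The wording needs tidying, but recruitment bias is not established.

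Finally, the completion rates used above are invented for scale, and nothing in the Protocol supports any particular gap. This is also true.

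**Conclusion.** The point holds as a conditional design weakness. The randomisation window overlaps the baseline diary, the text neither orders the two nor provides for concealment, and people who "will not complete the baseline diary (month 1) will be excluded from the analysis". Should allocation become known before 31 October 2007, both primary measures are open to bias that analysis cannot remove.

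The documents do not show that early disclosure happens, and the size of any effect is unknown. Under the assumed scenarios the bias in the responder rate is 1.1 to 2.9 points against a planned difference of 10. The excess loss in one arm is about 118 of 1178 under an assumed 10-point completion gap. Neither figure is a prediction. The sample size calculation is not affected. The change is worth making because it is cheap and closes a gap that cannot be repaired later.

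**What to change.** In the Schedule section, replace the two-month randomisation window with one of two statements:

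- Preferably: departments are randomised only after the October diary closes on 31 October 2007, and before the November instruction begins.
- At a minimum: if the list must be drawn earlier, allocation is not disclosed to departments, participants or instructors until the diary closes on that date.

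In the Study design section, replace the reference to the eligible population so that it matches the Schedule: the departments of consenting participants are randomised. The order of consent and allocation is then plain. In the Statistical analysis section, add that completion of the baseline diary will be reported by arm.

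The main cost is a shorter window for scheduling the first instruction sessions across up to 444 departments. The Intervention section spreads the first round over months 2-3, which eases this. Withholding an earlier list from those groups is the lighter option where the window is too tight. No additional data are collected under either option.

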## - Intervention

The instructions given to the participants of the experimental group (phase 1) and subsequently to the control group (phase 2) will be the following:

a) Relaxation exercise (once or twice a day):

Sit down on a comfortable armchair in a quiet room. Let the mandible drop in a position of maximum relaxation for about 10-15 minutes. Apply warm pads on cheeks and shoulders.

b) Posture exercises : 8-10 times every 2-3 hours

1) Keep an erect position with the tallons, the hips and the nuke against the wall. While the rest of the body does not move bring the shoulders into contact with the wall and release, rhythmically

[figure not shown]

2) While body and head are kept against the wall, make horizontal movements of the head, forwards and backwards

[figure not shown]

3) After having cupped the hands behind the neck, performs stretching movements of the head backward, with forward counterpressure from the hands. Relaxe after 2-3 seconds.

[figure not shown]

c) Visual feedback:

Place coloured labels in strategic sites at your workplace and at home to remind to keep muscle contraction at a normal level.

The programme will be explained and showed via web and by personal practical demonstrations by a team of trained clinicians three times during months 2-3, 4-5 and 6-7. The subjects in the study group will be asked monthly to rate their compliance level via web.

### **Controls**

In the control group during the first 7 months (phase 1), no Intervention will be performed nor any training instruction provided; the participants will be asked only to keep the diary everyday at months 1 and 7.

At beginning of month 8 (beginning of the second phase), the same Intervention will be administered to the control group, and diaries will be collected again at month 13.

### **Data collection**

All the participants will report in a diary, on a daily basis during months 1,7 and 13, the following information:

- presence or absence of the headache and neck and shoulder pain episodes
- severity (score from 1 to 5) of pain
- drug intake
- for women, menstruation days.

### **Sample size**

Of the eligible 11.780 workers, we will expect a participation rate of 20% of the sample.

The planned 2356 subjects (half per group) will provide a power of 0.95 to detect at least a difference of 10% ( $\alpha = 0.05$ , two-tails) in the proportion of symptomatic subjects (more than 4 days with pain during the baseline) that will have a significative reduction of pain frequency (assuming a prevalence of symptomatic subjects of 50%, a significative reduction ( $\geq 50\%$ ) in 20% of subjects in the Intervention group, a significative reduction in 10% of subjects in the Control group, and taking into account the cluster-randomized design of the study, assuming an intracluster correlation  $\rho = 0.15$ ).

### **Statistical analysis**

Subjects who will not give informed consent or will not complete the baseline diary (month 1) will be excluded from the analysis. The data will be analysed according to group distribution.

The **principal analysis** will be conducted between intervention and control group for the first phase of the study (months 1-7; Figure 1, line 1).

Analyses will be performed on subjects for which diaries will be completed for months 1 and 7.

The proportion of subjects with more than 50% reduction in headache days (and in neck and shoulder pain days) at the end of the study period will be assessed and compared between the two groups accounting for the cluster-randomized design of the study.

For each subject, the difference (Delta) in the frequency of symptoms between months 7 and the baseline (month 1) will be calculated; the Deltas between the two groups will be compared with parametric and non-parametric tests, where appropriate, taking into account the cluster-randomized design of the study.

Possible baseline differences between the study group and the controls will be evaluated with parametric and non-parametric tests where appropriate; unbalanced factors will be taken into account in the analysis, if necessary.

Explorative subgroup analyses will be performed by age, gender, severity, compliance, diagnosis, and type of job activity.

A **secondary analysis** (Figure 1, line 2) will be conducted within the intervention group, in order to evaluate the persistence of the efficacy of the intervention; the frequency of pain at months 13 will be compared with that observed at months 7.

A further secondary analysis will be conducted in order to compare the efficacy of the program in the intervention group (end of phase 1) and in control group (end of phase 2).

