## **Primary outcome**

The primary outcome measures are:

- the headache frequency
- the neck and shoulder pain frequency.

The efficacy of the Intervention will be measured in two ways:

- a) responders rate. End-point: proportion of subjects with more than 4 days with headache (neck and shoulder pain) during the baseline period that will have reduction in pain frequency of more than 50%, after 6 months.
- b) reduction in the frequency of pain. End-point: number of days per month with a headache (neck and shoulders pain), after 6 months.

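### The pain-frequency endpoint is tested on raw change scores, with baseline adjusted for only if found unbalanced; a prespecified baseline covariate would be more precise at almost no cost

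*Protocol*

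**What the plan says.** The Primary outcome section of the protocol measures efficacy in two ways: (a) a responder rate and (b) a reduction in pain frequency. Item (b) has as its endpoint the "number of days per month with a headache (neck and shoulders pain), after 6 months".

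The Statistical analysis section fixes how (b) is tested: "For each subject, the difference (Delta) in the frequency of symptoms between months 7 and the baseline (month 1) will be calculated". It continues: "the Deltas between the two groups will be compared with parametric and non-parametric tests, where appropriate, taking into account the cluster-randomized design of the study". Baseline frequency does not appear as a covariate. The same section plans to examine baseline differences with statistical tests, after which "unbalanced factors will be taken into account in the analysis, if necessary".

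The baseline count is available. The Schedule section asks every participant "to keep a diary (web-based) for one month (October 2007, baseline period"), and the Statistical analysis section restricts the analysis: "Analyses will be performed on subjects for which diaries will be completed for months 1 and 7". Every analysed subject therefore has a month 1 value.

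**The concern.** Comparing Deltas amounts to assuming that a subject with one more pain day at baseline has, on average, exactly one more at month 7. A one-month count of pain days is noisy, and high counts tend to fall back, so the real slope is likely to be below 1. Subtracting the whole baseline then over-corrects, with two consequences.

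- **Precision.** Part of the month 1 noise is carried into Delta, so the confidence interval for a primary endpoint is wider than the same data allow.
- **Chance imbalance.** If one group happens to start with more pain days, its Deltas will tend to look more favourable whatever the intervention does.

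The conditional clause on unbalanced factors may deal with the second consequence in some cases. It does not deal with the first, because adjustment gains precision whether or not the groups look balanced.

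**Working it through.** **1. The plan's own figure.** The Sample size section gives 2356 subjects (1178 per group), 50% symptomatic (589 per group), responder rates of 20% and 10%, an intracluster correlation of 0.15, two-sided alpha of 0.05 and power of 0.95. The mean cluster size is not stated; 2356/444 departments = 5.31 is used here.

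- Design effect: 1 + (5.31 − 1) × 0.15 = 1.646.
- Effective number per group: 589/1.646 = 357.8.
- Power for 20% against 10%: 0.964.

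This is close to the stated 0.95. The figure belongs to endpoint (a). No power is stated for endpoint (b), so nothing below overturns a number in the protocol.

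**2. Variance of the two analyses of endpoint (b).** Let s² be the variance of pain days, equal at months 1 and 7, and r the correlation between the two months.

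- Delta: 2(1 − r)s².
- Month 7 adjusted for month 1: (1 − r²)s².
- Ratio, adjusted to Delta: (1 − r²)/[2(1 − r)] = (1 + r)/2.

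The documents give neither r nor s, so r is an assumption shown as a range. The last column supposes that the Delta comparison had 80% power; power after adjustment is then Φ[(0.842 + 1.960)/√ratio − 1.960].

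| Assumed r | Delta (in s²) | Adjusted (in s²) | Ratio | Variance reduction | SE reduction | Power if Delta had 0.80 |
|---|---|---|---|---|---|---|
| 0.4 | 1.20 | 0.84 | 0.70 | 30% | 16% | 0.918 |
| 0.5 | 1.00 | 0.75 | 0.75 | 25% | 13% | 0.899 |
| 0.6 | 0.80 | 0.64 | 0.80 | 20% | 11% | 0.879 |
| 0.7 | 0.60 | 0.51 | 0.85 | 15% | 8% | 0.860 |
| 0.8 | 0.40 | 0.36 | 0.90 | 10% | 5% | 0.840 |
| 0.9 | 0.20 | 0.19 | 0.95 | 5% | 2.5% | 0.820 |

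Below r = 0.5, 2(1 − r) exceeds 1, so Delta is less precise than the month 7 count with no use of baseline at all.

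**3. Does clustering change this?** A simulation with normal data, 222 departments of 5 per group, intracluster correlation 0.15 and 3000 runs gave variance ratios of 0.70, 0.73, 0.80, 0.85 and 0.90 for r = 0.4, 0.5, 0.6, 0.7 and 0.8, in line with the formula. With r = 0.6 within departments but 0.9 between department means, the ratio was 0.90 where the formula at r = 0.6 gives 0.80. The gain shrinks but remains.

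**4. Sensitivity to imbalance.** A chance baseline difference d between groups shifts the expected difference in Delta by −(1 − r)d. If d equals one standard error of the baseline difference, the shift in units of Delta's own standard error is (1 − r)/√[2(1 − r)] = √[(1 − r)/2]. At r = 0.6, assumed equal within and between departments, this is √0.2 = 0.45; for a d of two standard errors it is 0.89.

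**The case against.** The strongest reply is that the protocol does foresee adjustment through its clause on unbalanced factors, and that computing Delta does not exclude a covariate. In a linear model, regressing Delta on group and baseline gives the same treatment estimate as regressing month 7 on group and baseline. All that is missing, on this view, is a firm commitment, which an unseen SAP could make. Part of this stands: the clause partly covers the imbalance argument, and it would be wrong to say that the plan ignores imbalance. But adjustment under the clause depends on tests of the data and on an undefined judgement of necessity, and it gives no precision when the groups look balanced. The protocol also names the comparison for this endpoint, so this is a choice made and not a detail left open.

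A reader might go further than the documents allow in four ways.

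- **That the endpoint is switched.** Item (b) is introduced as a reduction in pain frequency, and a month 7 minus month 1 difference is a natural measure of that. Under randomisation the group differences in mean Delta and in mean month 7 days have the same expectation.
- **That the Delta test is invalid.** It is unbiased under randomisation. The loss is in precision and in robustness to chance imbalance.
- **That the stated power is undermined.** The 0.95 concerns responders and is reproduced above.
- **That the responder model must also be adjusted, or a particular count model adopted.** No calculation here supports either.

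One caveat remains. The Schedule section places randomisation in September–October 2007 and the baseline diary in October 2007, so some month 1 entries may follow allocation. The instruction programme begins only in November, and Delta relies on the same month 1 count, so this is no reason to prefer the unadjusted comparison.

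**Conclusion.** The point holds as one of efficiency. The protocol fixes a valid but less precise comparison for a primary endpoint, although the baseline count exists for every analysed subject. Under equal variances the adjusted analysis is more precise for any r below 1. The direction is firm; the size is not. The variance reduction is 30% to 10% for an assumed r of 0.4 to 0.8, only 5% at 0.9, and less than the formula suggests if department means are more stable over time than individuals. The formula is a normal approximation for a count bounded by the length of the month. No figure stated in the protocol changes.

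**What to change.** For endpoint (b), and for headache and neck and shoulder pain alike, prespecify as the primary test a model of month 7 pain days with month 1 pain days as a covariate and with department clustering retained. The sponsor may keep Delta as the response if preferred, since a linear model gives the same treatment estimate. Include this covariate regardless of any baseline comparison, so that the test-then-adjust step no longer applies to it. Report the unadjusted Delta comparison as a sensitivity analysis.

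The cost is a change of wording and one extra model parameter. No further data are needed, and neither the sample size nor the diary schedule changes.

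### Covariates for the primary comparisons are to be picked by baseline tests with no stated criterion, and the randomisation strata are not named in those comparisons

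*Protocol*

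**What the plan says.** The Study design section of the protocol allocates departments at random, "stratified for professional groups and number of participants".

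The Statistical analysis section makes two between-arm comparisons at month 7: the proportion with more than a 50% reduction in pain days, and the change in pain days from month 1 (Delta). Each is made for headache and for neck and shoulder pain, and both are to allow for the cluster-randomised design. The two stratification factors are not named there. Type of job activity appears only in the list of exploratory subgroups.

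The only rule on covariates is in the same section. First, "Possible baseline differences between the study group and the controls will be evaluated with parametric and non-parametric tests where appropriate". Then, "unbalanced factors will be taken into account in the analysis, if necessary". No candidate factors, no threshold and no test of necessity are given.

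**The concern.** There are two linked problems.

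- **The covariate rule depends on the data.** Whether to adjust, and for what, is decided after the arms have been compared at baseline. A small p-value for imbalance does not show that a factor predicts pain, and a large one does not show that leaving it out is harmless. With two pain sites and two measures, this freedom applies to four primary comparisons.
- **The rule tends to pass over the factors that the design itself treated as important.** Stratified allocation tends to balance professional group and number of participants, so a test of imbalance will rarely select them. If they predict outcome, an analysis without them charges between-stratum variation to error although the allocation has already removed it from the treatment contrast.

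At stake are freedom from selection in the primary estimates and a modest amount of precision.

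**Working it through.** **1. Reproduce the protocol's own figure.** Inputs from the Sample size and Study design sections: "The planned 2356 subjects (half per group"), so 1178 per arm; half of them symptomatic, so 589 per arm; 444 departments; responder rates 0.20 and 0.10; intracluster correlation 0.15; two-sided alpha 0.05.

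- Participants per department: 2356 / 444 = 5.31.
- Design effect: 1 + (5.31 − 1) × 0.15 = 1.646.
- Effective symptomatic subjects per arm: 589 / 1.646 = 357.8.
- z = [0.10 × √357.8 − 1.96 × √(2 × 0.15 × 0.85)] / √(0.2 × 0.8 + 0.1 × 0.9) = (1.892 − 0.990) / 0.5 = 1.80, so power is 0.964, against 0.95 stated.
- By the continuity-corrected formula, 349 per arm are needed: 349 × 2 × 1.646 / 0.5 = 2298, against 2356 planned.

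The stated size reproduces, and nothing below changes it.

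**2. Chance flags from baseline testing.** The protocol does not list the factors to be tested. The Data collection section and the subgroup list suggest about nine: age, gender, severity, diagnosis, job type, headache days, neck and shoulder pain days, drug intake and menstruation days. If k independent factors are tested at 5% (level and independence assumed) in arms that differ only by chance, P(at least one flag) = 1 − 0.95^k:

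- k = 5: 0.23
- k = 9: 0.37 (expected number of flags 9 × 0.05 = 0.45)
- k = 10: 0.40
- k = 15: 0.54

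**3. Cost of leaving the strata out.** The protocol does not say how much of the between-department variance the strata explain, so the share s runs from 0 to 100%. The simulation worked on department means of an outcome with unit variance (a continuous approximation to response). Further assumptions were 444 departments, 8 strata, about 2.65 symptomatic subjects per department (1178 / 444) with Poisson spread, the stratum variance forming part of the 0.15, and 4000 runs per row. The planned effect is 0.10 / √(0.15 × 0.85) = 0.28 SD.

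| s | SE without strata | SE with strata | Ratio | Type I without / with | Power without / with |
|---|---|---|---|---|---|
| 0% | 0.0727 | 0.0727 | 1.00 | 0.051 / 0.051 | 0.967 / 0.968 |
| 20% | 0.0728 | 0.0709 | 1.03 | 0.047 / 0.052 | 0.977 / 0.979 |
| 50% | 0.0728 | 0.0680 | 1.07 | 0.034 / 0.048 | 0.978 / 0.983 |
| 100% | 0.0728 | 0.0627 | 1.16 | 0.025 / 0.050 | 0.981 / 0.991 |

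Monte Carlo error on a type I rate near 0.05 is √(0.05 × 0.95 / 4000) = 0.003.

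**4. Check by hand.** The variance of a department mean implied by the first row is V = (444 / 4) × 0.0727² = 0.587. Removing 0.15s gives a ratio of √[V / (V − 0.15s)]:

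- s = 0.2: √(0.587 / 0.557) = 1.03
- s = 0.5: √(0.587 / 0.512) = 1.07
- s = 1: √(0.587 / 0.437) = 1.16

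These agree with the table. The upper figures depend on the assumed spread of department size. With exactly 2.65 subjects in every department, V = 0.15 + 0.85 / 2.65 = 0.471, and the ratios become 1.03, 1.09 and 1.21.

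**The case against.** **The design wording may already cover the strata.** The protocol describes one design, clustered and stratified, and promises to account for it. Model terms are commonly left to an analysis plan, and one may exist. This stands to the extent that the protocol does not exclude the strata. A reader might infer that it does, but the text only fails to name them. The covariate rule is different: it is stated, so an analysis plan that named its covariates would have to replace that sentence, not fill a gap.

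**Baseline tests are not pointless here.** A reader might infer that in a randomised trial they can detect nothing but chance. The documents do not support that for this analysis set. It is limited to subjects with diaries for months 1 and 7, month 7 comes after the intervention, and the Schedule section lets the September-October randomisation overlap the October baseline diary. Some imbalance among completers could therefore be systematic, and allocation by department does not guarantee balanced strata among individual completers. This is a good reason to look at balance. It does not rescue a test without a criterion, because a non-significant difference does not show that confounding is absent.

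**The harm to the standard error is small and conservative.** This stands in full. It is zero if the strata do not predict outcome, and it does not raise the false-positive rate.

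**Strata terms do not belong everywhere.** This also stands. Stratum main effects do nothing for the within-arm comparison of month 13 with month 7. Non-parametric tests, which the protocol allows, do not take covariates directly. Baseline frequency already enters Delta and the responder definition, but subtracting a baseline is not the same as adjusting for it.

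**Conclusion.** The point holds, chiefly for the covariate rule. As written, adjustment of the four primary comparisons can be settled after the data are seen, on imbalance and with no criterion. The bias that this could cause is not quantified, because the protocol does not fix how the choice would be made.

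The point about the strata is secondary. If they explain 20 to 50% of between-department variance, leaving them out makes the standard error about 3 to 7% too large (0 to 16% over the full simulated range). Type I error then lies between 0.05 and 0.025, and the power loss is about 1 point or less. These figures rest on the assumed share, number of strata and spread of department size. They also assume planned recruitment; the power loss is small partly because the planned power is already near its ceiling.

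A reader might infer that the trial is underpowered or its primary test invalid. Neither follows: the stated power reproduces (0.964 against 0.95) and the error is on the cautious side. Nor do the documents support a long list of tested factors in which a chance flag is to be expected. About nine candidates can be identified, with 0.45 flags expected by chance.

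**What to change.** In the Statistical analysis section:

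1. For the between-arm comparisons at month 7 (responder proportion and pain days, each for headache and for neck and shoulder pain), specify a cluster-adjusted model with the randomisation strata (professional group and number of participants, as categorised for the allocation) and the baseline pain-day count as prespecified covariates. Delta can be kept: in a linear model with baseline as a covariate, the treatment estimate is the same whether the outcome is Delta or month 7 days.
2. Replace the baseline tests and the conditional adjustment rule with a descriptive report of baseline balance by arm, including among subjects with diaries for months 1 and 7.
3. Treat any further adjustment as a labelled sensitivity analysis with covariates named in advance.

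The within-arm comparison of month 13 with month 7 needs no strata terms.

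The cost is a few sentences. The strata are needed for the allocation anyway, baseline pain days come from the month 1 diary, and the sample size does not change.
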